**Patients**					
Medical history	√				
Physical examination	√	√	√	√	
Laboratory examination	√			√	
Sign informed consent		√			
Randomization		√			
**Intervention and control**					
HCI group	16 sessions of acupuncture				
LOI group					
MC group	5 mg mosapride citrate tablet, three times a day				
**Outcomes**					
Number of defecating events per week		√	√	√	√
Shape and properties of stool		√	√	√	√
Intensity of defecating difficulty		√	√	√	√
PAC-QOL		√	√	√	√
SF-36		√		√	
SAS		√	√	√	
SDS		√	√	√	
The time of the first spontaneous defecation					
**Safety assessment**					
Safety of electro-acupuncture		√	√	√	
Adverse event		√	√	√	
**Trial evaluation**					
Patient’s compliance				√	
Rates of dropouts and withdrawals				√	

*HCI* high current intensity; *LCI* low current intensity; *PAC-QOL* Patient Assessment of Constipation Quality of Life; *SF*-36 MOS item Short Form health survey; *SAS* Self-Rating Anxiety Scale; *SDS* Self-rating Depression Scale.

### Patient safety

All patients participating in this trial will receive routine blood, urine, and stool tests as well as an electrocardiogram, blood biochemical tests (ALT, AST, BUN, and Scr), and colonoscopy prior to randomization. These tests will help identify and exclude patients who have serious heart, liver, and kidney diseases or other severe diseases. To exclude pregnant women, urine HCG or blood β-HCG will be tested for possible pregnancy. The patients will receive routine blood, urine, and stool tests after completing the treatment. These tests will help assess the risks associated with acupuncture or mosapride treatment.

### Quality control and trial monitoring

To guarantee the quality of the study, all acupuncturists and researchers will be required to undergo special training, including theoretical and practical lessons. They must master all of the details of this trial before performing it. For instance, they will be trained on how to use the randomization method, fill in the case report form, manipulate the needles and electro-acupuncture apparatus, etc. After attending all of the training classes and passing the training test, the researchers will be qualified to perform this trial. During the trial, all adverse events, including broken needles, bleeding, hematoma, fainting, serious pain, and local infection, are to be recorded during the treatment and the follow-up period. Serious adverse events will be immediately reported to the principal investigator. All details will be recorded, and rescue procedures will be initiated at once.

To ensure the quality of this trial, clinical monitor designated by the principle investigator will check all of the details of the process at regular intervals. Moreover, the monitor will check the authenticity of the data from each research centers.

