### Interventions

The total study period will be 9 weeks for each patient, 1 week for baseline, 4 weeks for treatment, and 4 weeks for follow-up (5 to 8 weeks after randomization at 0 week) (Figure 2). Participants in the electro-acupuncture groups will receive 16 acupuncture treatments: five times per week (once a day for 5 days continuously, followed by a 2-day interval) during the first 2 weeks and three times per week (once every 2–3 days) during the following 2 weeks. Each session will last 30 min.

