**Figure 2 F2:**
[figure not shown]
The total study period and the timepoint of evaluation.

Acupoints Quchi (LI11) and Shangjuxu (S37) will be used on both sides, which is consistent with the principles of traditional acupuncture theories. Sterile, disposable needles made in Shanghai, China, will be used in this trial. The needles will be 25 to 50 mm in length and 0.3 mm in diameter. De qi sensation will be achieved in the acupuncture groups through lifting and thrusting movements combined with twirling and rotating the needles. After being acupunctured, the points will be punctured again using auxiliary needles 2 mm lateral to the first needle, to a depth of 2 mm, without manual stimulation. The auxiliary needles will be of the same brand, being 13 mm in length and 0.18 mm in diameter. The acupuncture needle and auxiliary needle of each point will be connected to form a circuit containing a HANS-200E stimulator (Nanjing Jisheng Co., China) for 30 min. The reason behind using the auxiliary needle is to guarantee the current confined in each acupoint. The stimulation parameters of electro-acupuncture in the high current intensity group will be an alternating wave with a frequency of 2/50 Hz; the current will be strong enough to reach the patients’ tolerance threshold value (1.0-1.8 mA, based on preliminary results). The frequency will be the same in the low current intensity group; while the current (0.2-0.7 mA) applied to this group will be relatively weak, it will be clearly perceived by the participants.

Participants in the control group will be orally administered 5 mg mosapride citrate tablets three times a day for 4 continuous weeks.

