As for the rationale of acupoint selection, we screened acupoints through a systematic review of ancient books, acupuncture textbooks, and published articles. Meetings were held to further screen for a standardized acupuncture protocol and reach consensus among acupuncture experts in China. Based on the theory of acupuncture, Back-Shu and Front-Mu points (short for Shu-Mu points), which are located in the lower back or abdomen of the body, are the classic combination for the treatment of internal organ disease. Additionally, Hepoint (Quchi, LI11) and Lower Hepoint (Shangjuxu, S37) of the large intestine meridian are also positive points, which are respectively situated in the upper and lower limbs of the body. Nei Jing states: ‘He points are the best points to treat internal organ’s disease.’ However, our preliminary results have indicated that the effect of Shu and Mupoints in rats mainly excite gastrointestinal motility, while the effect of acupuncture in either Quchi or Shangjuxu is characterized by inhibiting motility. Therefore, the purpose of this study is to further validate the effect of acupuncture in Hepoints (Quchi and Shangjuxu) on functional constipation, as well as the relationship between the stimulation intensity and the resulting effect.

In this trial we are using mosapride as a positive control group rather than sham acupuncture as a negative control group. This setting is mainly based on the fact that any surface stimulation at acupoints, such as acupressure, can cause a physiological reaction or effect [13,14]. Thus, it is difficult to set a real non-active control for clinical acupuncture trials. As for mosapride, it is a gastroprokinetic agent that acts as a selective 5HT4 agonist. Mosapride accelerates gastric emptying and is used for the treatment of acid reflux, irritable bowel syndrome and functional dyspepsia [15]. Thus, mosapride also has the potential to treat functional constipation [16]. We therefore chose mosapride citrate as a positive drug control.

This study will provide significant evidence for the application of acupuncture in functional constipation and will be the first to identify a suitable parameter of stimulation for treatment.

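### Adverse event capture risks differing by arm: acupuncture patients meet staff at 16 sessions, mosapride patients only at the common assessments, and no arm-neutral symptom enquiry is stated

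*Protocol article*

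**What the plan says.** **Contact.** Under Interventions, "Participants in the electro-acupuncture groups will receive 16 acupuncture treatments: five times per week" in the first two weeks, then "three times per week (once every 2–3 days) during the following 2 weeks". The comparator is described in one sentence: "Participants in the control group will be orally administered 5 mg mosapride citrate tablets three times a day for 4 continuous weeks". No attendance is stated for that arm beyond the assessments common to all arms, which Table 1 places at 0, 2, 4 and 8 weeks.

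**What is recorded.** Quality control and trial monitoring says "all adverse events, including broken needles, bleeding, hematoma, fainting, serious pain, and local infection, are to be recorded", during both treatment and follow-up. Table 1 has two safety rows. One is labelled "Safety of electro-acupuncture"; the other is a general adverse event row not limited to any arm. As the extracted table reads, both are ticked at 0, 2 and 4 weeks.

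**Laboratory safety.** Under Patient safety, all patients have routine blood, urine and stool tests after treatment. The stated purpose covers the risks of acupuncture and of mosapride.

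**Common instrument.** Under Outcome measures, all participants keep a constipation diary from one week before randomization to week 8.

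**The concern.** What is recorded as an adverse event depends on how often a patient is in front of staff and on what is asked. Both appear to differ by arm. A brief or mild symptom has many more occasions to be mentioned or noticed in someone attending 16 sessions than in someone seen at two or three assessments. The examples given to staff (broken needles, hematoma, local infection and so on) direct attention to the procedure, and so does the dedicated table row.

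The trial compares electro-acupuncture with a drug, so event counts by arm are a natural output and will be read side by side. If detection differs, equal true rates could look unequal, and part of any real difference could be hidden or exaggerated. The likely tendency is relatively more recorded events on acupuncture and fewer on mosapride.

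**Working it through.** **1. Sessions.** 5 × 2 + 3 × 2 = 16, which reproduces the stated number of treatments.

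**2. Contacts per arm during treatment.** Acupuncture: 16 sessions. Mosapride: 2 common assessments after the start of treatment (weeks 2 and 4), or 3 if the 0-week tick is counted. Ratio: 16/3 = 5.3 to 16/2 = 8. The week-8 visit is common to all arms and falls after treatment.

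**3. What unequal contact could do (illustration only).** Let q be the chance that one contact elicits a given event. With k independent contacts, P(recorded) = 1 − (1 − q)^k. The documents give no q, so a range is assumed.

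| q (assumed) | 16 contacts | 3 contacts | 2 contacts | Ratio 16 v 3 | Ratio 16 v 2 |
|---|---|---|---|---|---|
| 0.05 | 0.560 | 0.143 | 0.098 | 3.9 | 5.7 |
| 0.10 | 0.815 | 0.271 | 0.190 | 3.0 | 4.3 |
| 0.20 | 0.972 | 0.488 | 0.360 | 2.0 | 2.7 |
| 0.50 | 1.000 | 0.875 | 0.750 | 1.1 | 1.3 |

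A different assumption, a fixed recall window before each contact, lands in the same range. With 3 days, acupuncture contacts cover about 28 of 28 days and two mosapride contacts cover 6 of 28, a ratio of 28/6 = 4.7. With 7 days it is 28/14 = 2.0.

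Both calculations treat every session as an occasion on which an event can come to light. The article does not say that adverse events are asked about at each session. The ratios show what could happen under the assumptions and do not estimate what will.

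**4. Does any stated provision equalise symptom detection?**
- The requirement to record all events and the general adverse event row set the scope for every arm. They do not change the number of contacts or the prompts.
- The post-treatment laboratory tests cover both treatments, but they do not pick up symptoms such as nausea or dizziness.
- The diary is identical across arms and runs to week 8. As described it is a constipation diary, and no adverse event item is mentioned.

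**5. A neighbouring mismatch.** The text has adverse events recorded in follow-up, whereas neither safety row in Table 1 carries a week-8 tick as extracted. These two places must be reconciled.

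**The case against.** The case on the other side is substantial, and much of it stands.

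- **The list is illustrative.** It follows a requirement to record all events and excludes no arm. Bleeding, fainting and serious pain can also occur in a patient taking tablets. A reader might infer that only needling events are sought; the text does not support that.
- **The mosapride arm is covered.** The general adverse event row applies to it, and the laboratory tests are expressly meant for either treatment. A reader might infer that drug safety is not monitored. That is wrong; what is absent is a mosapride-named row.
- **Worsening constipation is measured.** The Discussion reports rat results in which "the effect of acupuncture in either Quchi or Shangjuxu is characterized by inhibiting motility", and these are the points used here. A reader might infer that this potential harm goes unobserved. It does not: defecation frequency is the primary outcome, and stool properties and defecating difficulty are secondary outcomes, all collected equally in all arms.
- **No safety comparison is planned in the text.** The objectives concern effectiveness and current intensity, and Statistical analysis states no safety hypothesis. To call the safety comparison biased, or wrong in direction, goes beyond the document.
- **An article condenses.** The exact wording of the adverse event form may sit in the full protocol or the case report form. Unequal contact is also inherent in comparing needling sessions with tablets.

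The last point limits how hard the concern can be pressed, but does not remove it. The contact schedule, the choice of examples and the row label are stated in the article, and they all point the same way. That unequal contact is inherent is itself a reason to base by-arm counts on an instrument independent of the sessions.

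**Conclusion.** The concern holds as a risk of differential ascertainment. The document fixes 16 staffed sessions against 2 or 3 common assessments during treatment, procedure-leaning examples, and a treatment-specific safety row for one modality only. The provisions that cover mosapride do so in scope and in laboratory testing; they do not equalise the detection of symptoms.

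The size cannot be determined from the documents. Ratios of about 1.1 to 5.7 follow from assumed per-contact detection of 0.50 down to 0.05, on the further assumption that each session can bring an event to light. If detection per contact is high, the distortion is small. The point is a worthwhile, inexpensive improvement to how by-arm event counts are collected. It does not touch the efficacy comparison.

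**What to change.** 1. Add one arm-neutral open question on adverse events, with a short common symptom checklist (for example abdominal pain, diarrhea, nausea, dizziness, worsening constipation), to the diary all participants already keep to week 8. Review it at the shared visits in the same way in all three arms.
2. Base any between-arm presentation of event rates on these commonly collected events. Report needling events observed at sessions separately and descriptively for the acupuncture arms.
3. Rename the electro-acupuncture safety row in Table 1 *Safety of study treatment*, and reconcile the table with the text on recording in follow-up.

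**Cost.** A small diary and case report form change and slightly more data entry, with no extra visit. Recorded event counts in the mosapride arm may rise. The benefit reaches only participants not yet recruited: Trial status gives 123 recruited by 15 March 2013 out of a planned 243, so 243 − 123 = 120, about half, remained at that date. Presentations based on the new item should be limited to participants who received it.

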### Trial evaluation

The trial evaluation will include patient compliance and the ratio of dropouts or withdrawals, which will be measured at the 4th week after randomization, and their reason will be recorded in time.

### Statistical analysis

Statistical analyses will be undertaken by the Department of Epidemiology and Biostatistics, School of Public Health, Tongji Medical College, Huazhong University of Science and Technology. Baseline characteristics of the subjects will be described by descriptive analysis and analyzed by analysis of variance, *χ*^2^-test, and others. With regard to the effects of intervention, the *χ*^2^-test will be applied to compare frequencies between groups, such as the number of defecating times per week; analysis of variance will be performed for comparison of continuous parameters between the groups (α = 0.05). All of the analyses will be based on both an intention-to-treat analysis (ITT) and a treated-per-protocol analysis (TPP).

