### Randomization and blinding

The participants will be randomly assigned to three groups through complete randomization at a 1:1:1 ratio equally among the three centers: high current intensity group, low current intensity group, and mosapride citrate control group. Therefore, each group in each center will have 27 participants. The randomization sequence will be generated using R2.0 software. A designated researcher will prepare the assignments in opaque envelopes in sequence.

The acupuncturists will only know of the grouping scheme just prior to the treatment to ensure that the trial will be as blinded as possible. The researchers will not be permitted to predict a patient’s assignment or change it after the patients are randomized. Blinded evaluation (the curative effect will be evaluated by a third party who does not know the grouping) and blinded statistical analysis will be emphasized during the data collection and analysis stage.

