### Outcome measures

All of the participants in this trial will be asked to update constipation diaries from 1 week before randomization to 8 weeks after randomization. Only when they are eligible in the baseline phase for this study will the participants be asked to make diary entries from 0 to 8 weeks after randomization.

The primary outcome in this trial is the number of defecating events per week at baseline and at the 2nd, 4th and 8th week after randomization (Table 1 and Figure 2). Secondary outcomes include the following five aspects: shape and properties of stool, intensity of defecating difficulty, Patient Assessment of Constipation Quality of Life (PAC-QOL), MOS item Short Form health survey (SF-36), Self-Rating Anxiety Scale (SAS), and Self-rating Depression Scale (SDS). The first three of the secondary outcomes will be measured at baseline and at the 2nd, 4th and 8th week after randomization. The other secondary outcomes will be measured at baseline and at the 2nd and 4th week after randomization, although SF-36 will be measured only before randomization and 4 weeks after randomization. Additionally, the time of the first spontaneous defecation (from the end of the first intervention to the first spontaneous defecation) will be recorded.

**Table 1 T1:** Trial process

	**Baseline**	**Treatment**			**Follow-up**
**Time**	−1w	0w	2w	4w	8w
**Assessment**		1st	2nd	3rd	4th

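### The analysis section does not say whether stool shape and defecating difficulty go to chi-square or ANOVA: chi-square would discard any ordering, and neither test as named uses the baseline value

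*Protocol article*

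**What the plan says.** Protocol article, Statistical analysis. For the effects of intervention, a chi-square "test will be applied to compare frequencies between groups" is planned, with the weekly stool count as its only example; for the rest, "analysis of variance will be performed for comparison of continuous parameters between the groups (α = 0.05"). No third method is named for treatment effects. The same section has an open-ended list of tests, but it belongs to a different sentence: "Baseline characteristics of the subjects will be described by descriptive analysis and analyzed by analysis of variance", chi-square and others. That latitude covers baseline description only.

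Protocol article, Outcome measures. The secondary outcomes begin with "shape and properties of stool, intensity of defecating difficulty". On timing: "The first three of the secondary outcomes will be measured at baseline and at the 2nd, 4th and 8th week after randomization". Table 1 shows the same four assessments. Neither place gives a scale, a number of grades or a scoring rule for these two outcomes, and neither links them to one of the two tests.

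**The concern.** Stool shape and intensity of difficulty are usually recorded as ordered grades. A reader applying the two-way rule could well put them under frequencies, since shape is not obviously a continuous measure and the section's own example of a frequency is a weekly count. A Pearson chi-square on an arm-by-grade table treats the grades as interchangeable labels. A steady shift towards better grades is then spread over many degrees of freedom, and the test returns neither direction nor size of effect.

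A second point does not depend on which test is meant. Both outcomes are measured before treatment, yet neither a chi-square on the follow-up table nor a one-way ANOVA uses that measurement. These two outcomes are the main symptom evidence beside the stool count, so avoidable loss of precision matters somewhat, although the primary outcome is not affected.

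**Working it through.** **Inputs from the article.** Three arms, 1:1:1 (Randomization and blinding). 71 evaluable per arm, α = 0.05, β = 0.10 (Sample size). Assessments at baseline and weeks 2, 4 and 8 (Outcome measures).

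**Inputs assumed, because the article gives none.** 4, 5 or 7 ordered grades; equal control-group probabilities over the grades; a proportional-odds shift of both acupuncture arms against mosapride with odds ratio 1.5 to 2.5; a latent baseline-to-outcome correlation of 0.4 or 0.6.

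**Step 1. The plan's own figure.** The article gives no power for these outcomes; its only figure is 71 per arm for the weekly count. With difference 4.0 − 2.6 = 1.4 and the simple mean SD (2.2 + 3)/2 = 2.6, n = 2 × (1.96 + 1.2816)² × 2.6² / 1.4² = 72.5, so 73. With the root-mean-square SD of 2.63, n is 75 and power at 71 is 88.7%. So 71 is reproduced to within a few patients and is used below.

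**Step 2. Chi-square against methods that keep the order.** Simulated power, three arms, 71 per arm, 2,000 runs per scenario:

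| Grades | Odds ratio | Chi-square | Kruskal-Wallis | ANOVA on scores |
|---|---|---|---|---|
| 4 | 1.5 | 17% | 26% | 26% |
| 4 | 2.0 | 47% | 65% | 66% |
| 4 | 2.5 | 73% | 88% | 89% |
| 7 | 1.5 | 14% | 29% | 28% |
| 7 | 2.0 | 36% | 67% | 67% |
| 7 | 2.5 | 61% | 90% | 90% |

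A separate run at odds ratio 2.0 gave chi-square 47%, 42% and 35% for 4, 5 and 7 grades, against about 65 to 68% for the other two tests. Skewed control distributions gave the same pattern.

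**Step 3. Why the gap arises.** The chi-square has (3 − 1)(K − 1) degrees of freedom: 6, 8 and 12 for K = 4, 5 and 7. A test that keeps the order has 2. A noncentrality of 7.07 gives 66% power on 2 degrees of freedom. The same noncentrality gives 47% on 6, 42% on 8 and 35% on 12, which agrees with the simulation.

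**Step 4. The unused baseline.** Adjusting for a baseline value with correlation ρ multiplies residual variance by 1 − ρ², so noncentrality is divided by it. For an F test with 2 and 210 degrees of freedom, 66% power corresponds to noncentrality 7.17.
- ρ = 0.4: 7.17 / 0.84 = 8.54, power about 74%.
- ρ = 0.6: 7.17 / 0.64 = 11.20, power about 85%.

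These are upper values, because a baseline recorded in grades carries less information than the latent scale. Simulation with graded baselines gave 70 to 74% and 79 to 84%, against about 66% unadjusted. The gain is 4 to 8 points at 0.4 and about 14 to 18 points at 0.6, with the unadjusted power varying by a point or so between scenarios. A two-arm check with 68 per arm and 5 grades agrees: 63% to 68% at 0.4, and 62% to 77% at 0.6.

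**The case against.** The strongest reply is that the article never sends these outcomes to chi-square. Its only example of a frequency is the weekly number of defecations, and no scale is given, so even their being graded is an inference. Diaries are kept throughout, so averaged scores analysed by ANOVA are a plausible plan, and Step 2 shows that ANOVA on scores matches a rank test within about a point. This stands. A reader might infer that the plan will lose the order of the grades and much of its power. The document does not support that: the loss occurs only on the chi-square reading.

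A second reply is that a condensed article may leave the test for a secondary outcome, and any covariates, to an analysis plan that is not shown. This also stands in part: the lack of a named ordinal method is not in itself an error. However, the sentence on intervention effects is worded as a closed pair of methods, and neither of them, as named, adjusts for baseline. ANOVA could be run on change from baseline, but that is no substitute. With equal variances its variance factor is 2(1 − ρ), which is 1.2 at ρ = 0.4 (worse than no adjustment) and 0.8 at ρ = 0.6, against 0.84 and 0.64 for ANCOVA.

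A third reply is that the sizes rest on assumed scales and effects. That is true. At odds ratio 1.5 with 4 grades the chi-square gap is only about 9 points. The direction was the same in every scenario with a real effect.

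**Conclusion.** The point holds in two parts, both minor.

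- **Conditional.** If stool shape and difficulty are graded and compared by unordered chi-square, order is ignored and power falls: at an assumed odds ratio of 2.0, from about 65% to 47% with 4 grades and from about 67% to 35% with 7. If they are scored and analysed by ANOVA, this loss does not occur. The article does not say which applies.
- **Under either reading.** The baseline value is collected but unused by the tests as named. The cost is roughly 4 to 8 points of power at an assumed correlation of 0.4 and about 14 to 18 points at 0.6.

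The number of grades, their distribution, the odds ratios and the correlations are all assumptions. The outcomes are secondary, and nothing here bears on the sample size or on the validity of the primary comparison.

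**What to change.** State in the analysis plan the scale of each outcome and which direction is better. If the best stool grade lies in the middle of the scale, define the outcome as distance from it. Then state that stool shape and defecating difficulty will not be compared by unordered chi-square, but by a model with arm, centre and the baseline value: proportional odds if graded, ANCOVA if scored. Report an odds ratio or mean difference with its 95% confidence interval at weeks 2, 4 and 8, for each acupuncture arm against mosapride and for high against low intensity. An unadjusted rank test is not an adequate alternative, since it also ignores baseline.

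The cost is a few sentences and a little analysis work; no new data or visits are needed. The one drawback is that the proportional-odds assumption must be checked, with ANCOVA on scores as the stated fallback. Trial status gives 123 participants recruited by 15 March 2013 against a planned 243, so at that date the wording could still be settled before the final analysis.

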### Sample size

Sample size calculation is based on a study by Camilleri:A placebo-controlled trial of prucalopride for severe chronic constipation [J]. N Engl J Med, 2008, 358 (22): 2344–2354 [11]. After drug treatment, the average defecation rate of patients with functional constipation was 2.6 times per week, with a standard deviation of 2.2. Furthermore, there was a 1.4-fold difference in the clinical effects between the drug and the placebo. Therefore, based on this study along with our preliminary test, the mean defecating frequency is 4.0 after acupuncture treatment, with a standard deviation of 3. To detect this difference, we need a minimum total sample size of 213 [71 for each group (α = 0.05, β = 0.10)] [12]. To allow for a loss of 15%, a total sample size of 243 (81 for each group) is required.

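### The primary outcome, a per-patient weekly defecation count sized on means and SDs, is assigned to a chi-square test

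*Protocol article*

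**What the plan says.** Outcome measures defines the endpoint: "The primary outcome in this trial is the number of defecating events per week at baseline and at the 2nd, 4th and 8th week". Each patient contributes a number, taken from a diary.

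Statistical analysis divides the methods in two. The chi-square test "will be applied to compare frequencies between groups, such as the number of defecating times per week". In contrast, "analysis of variance will be performed for comparison of continuous parameters between the groups (α = 0.05"). The primary outcome is therefore the named example for chi-square and is set apart from the method for means.

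Sample size treats the same variable as quantitative. After drug treatment "the average defecation rate of patients with functional constipation was 2.6 times per week, with a standard deviation of 2.2", and "the mean defecating frequency is 4.0 after acupuncture treatment, with a standard deviation of 3". From these it derives a "minimum total sample size of 213 [71 for each group (α = 0.05, β = 0.10")].

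Nowhere does the article define a responder, a cut-off or count categories.

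**The concern.** The word frequency seems to have been used in two senses: how often a patient defecates, and how many patients fall in a cell of a table. A Pearson chi-square test needs the second. To use it on a weekly count, the analyst must choose a construction that the article does not give:

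- tabulate patients by count value, which ignores the ordering of the counts;
- cut the count into two classes, which discards information;
- compare total defecations per arm, which treats every bowel movement as independent with Poisson variance.

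The first two do not deliver the 90% power on which the trial was sized. The third does not hold the 5% error rate. The choice is also open, so it could be made after the data are seen. None of the three tests the difference in mean weekly defecations that the sample size was built on.

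**Working it through.** **Inputs (Sample size).** Drug arm: mean 2.6, SD 2.2. Acupuncture: mean 4.0, SD 3. Difference 4.0 − 2.6 = 1.4. α = 0.05 (taken as two-sided; the article does not say), β = 0.10, 71 evaluable patients per group.

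**Step 1: reproduce the 71.** For two means, n per group = 2·SD²·(1.96 + 1.2816)²/1.4².

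- Average SD, (2.2 + 3)/2 = 2.6: n = 73.
- Root-mean-square SD, √((4.84 + 9)/2) = 2.63: n = 75.
- Three-group ANOVA with means 2.6, 4, 4 and SD 2.63: n = 69.

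None gives exactly 71, but a comparison of means comes close. Its power at 71 per group with SD 2.63 is Φ(1.4/(2.63·√(2/71)) − 1.96) = Φ(1.21) = 88.7%. The planned 90% thus belongs to a comparison of means.

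**Step 2: a model for the counts.** The article gives no distribution. I assume negative binomial counts with the stated means and SDs: size = mean²/(variance − mean), giving 6.76/2.24 = 3.02 for the drug arm and 16/5 = 3.2 for acupuncture.

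**Step 3: chi-square on a dichotomy.** Under that model the proportion with 3 or more per week (an assumed cut-off) is 43.3% on drug and 63.8% on acupuncture. With average proportion 0.536:

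- null SE = √(0.536·0.464·2/71) = 0.0837;
- alternative SE = √((0.433·0.567 + 0.638·0.362)/71) = 0.0819;
- power = Φ((0.2043 − 1.96·0.0837)/0.0819) = Φ(0.49) = 69%;
- 90% power would need 124 per group.

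Other cut-offs:

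| Cut-off (per week) | Drug | Acupuncture | Power, 71 per group | n per group for 90% |
|---|---|---|---|---|
| ≥1 | 84.7% | 92.5% | 31% | 341 |
| ≥2 | 63.3% | 79.3% | 56% | 166 |
| ≥3 | 43.3% | 63.8% | 69% | 124 |
| ≥4 | 27.9% | 48.9% | 73% | 112 |
| ≥5 | 17.2% | 36.0% | 72% | 114 |
| ≥6 | 10.2% | 25.8% | 68% | 127 |

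A normal model cut at 3 gives nearly the same answer as the negative binomial: 68% power and 126 per group.

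**Step 4: chi-square on arm totals.** If events are treated as Poisson, the statistic is inflated by φ = variance/mean. From the stated figures φ = 2.2²/2.6 = 1.86 and 3²/4.0 = 2.25. The true error rate is the probability that a chi-square variable exceeds the critical value divided by φ.

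- Three arms (2 df): exp(−5.99/(2·1.86)) = 20% and exp(−5.99/(2·2.25)) = 26%.
- Two arms (1 df): P(|Z| > 1.96/√1.86) = 15% and P(|Z| > 1.96/√2.25) = 19%.

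**Step 5: simulation.** 4,000 runs, 71 per arm, negative binomial counts. Power uses means 2.6 and 4.0 (two arms) or 2.6, 4.0 and 4.0 (three arms). Type I error covers a common mean of 2.6 and of 4.0.

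| Analysis | Power, 2 arms | Power, 3 arms | Type I error |
|---|---|---|---|
| ANOVA on counts | 88.7% | 91.7% | 5.0–5.4% |
| Chi-square, every count value a category | 36.1% | 33.9% | 3.1–3.2% |
| Chi-square, 8 or more pooled | 55.3% | 52.0% | 4.1–4.6% |
| Chi-square, cut at ≥3 | 69.6% | 72.4% | 4.8–5.5% |
| Chi-square on arm totals | not meaningful | not meaningful | 14.6–18.7% (2 arms); 20.8–26.4% (3 arms) |

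Power is not shown for arm totals because that test does not hold its level.

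**The case against.** The strongest reply is that a chi-square statistic need not be a Pearson chi-square on a table. Kruskal-Wallis and mean-score tests also refer to a chi-square distribution and use the ordering or values of the counts. In simulation at 71 per arm, Kruskal-Wallis had 86–89% power and a mean-score test 88–91%, both with type I error of about 5–6%. So a test of this family could be sound. That stands, but the article names none of these. It names the chi-square test alone and contrasts it with the method for continuous variables, so the plain reading is the Pearson test.

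A second reply is that the phrase is a loose example in a condensed article and that the full analysis plan may settle the matter. Detail left to such a plan would be no fault. Here, however, a method is stated, and the example is the primary outcome itself. A plan that used analysis of variance would contradict the published text, so the two would still need reconciling.

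Third, the figures depend on the construction. The error inflation applies only to arm totals, which nothing in the text singles out. The power figures depend on an assumed distribution, cut-off and pooling. This is right, and the figures should be read as conditional.

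Finally, choosing a chi-square test does not prevent the authors from also reporting means with a confidence interval. That is also right, but such an interval would not correspond to the test that decides the result.

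**Conclusion.** The concern holds, and the text should be corrected before analysis. The stated test does not fit the primary outcome and does not match the basis of the sample size. If patients are the unit, power falls from about 89–92% to 34–55% (count categories) or 31–73% (dichotomy, cut-offs 1 to 6). If bowel movements are the unit, the 5% error rate becomes about 15–19% with two arms and 20–26% with three.

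The power figures rest on negative binomial counts, two-sided α and the stated means and SDs. The error inflation needs only the stated SDs and independent patients, not the negative binomial shape. The mismatch itself rests on no assumption: it can be read directly from the three sections.

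**What to change.** In Statistical analysis, remove weekly defecations as the example for the chi-square test. State that the per-patient weekly count is analysed as a quantitative outcome, by analysis of variance or a linear model on the count or its change from baseline, with the between-group difference and its 95% confidence interval. Analysis of variance is already in the section and gives the planned power. Negative binomial regression with robust standard errors, reporting a rate ratio, is an acceptable alternative but not a necessary one. Keep chi-square for variables that are truly categorical, such as sex or the occurrence of an adverse event.

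The cost is one sentence in the protocol or analysis plan, with no new data and no extra patients. Trial status reports 123 recruited at 15 March 2013 against a target of 243, so at that date the correction could still be made before analysis.
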